#### Subgroup analyses

A subgroup analysis will be conducted on those mothers undergoing a trial of labour, excluding those who had a planned pre-labour cesarean delivery. Parity interaction terms will be omitted (and if they were significant in the main analysis, only nulliparous mothers will be analysed, as was done for the main analysis). Stepwise backward elimination will be conducted from the beginning, including either pre-pregnancy BMI or delivery BMI, whichever was chosen in the main analysis based on predictive value there.

#### Sensitivity analysis

(1)The primary analysis will be replicated using gestational weight gain instead of gestational BMI gain.(2)If multiple imputation is used, then the final multivariate fitted model from the imputed datasets will be replicated in the complete data for comparison.

We will report the results for the sensitivity analysis in pounds as well as kg.

## Protocol validation

We conducted an exploratory analysis of the US birth data for 2022 to inform modelling decisions. Linearity was tested for continuous variables by plotting variable quantiles against the natural logarithm of the cesarean section rate, with Wilson confidence intervals. Based on these analyses, maternal height and maternal age were linearly associated with cesarean section and will be modelled in natural units.

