### Secondary outcomes

Secondary outcomes were clinically relevant outcomes available in the dataset.

Maternal
-Third- or fourth-degree perineal laceration-Instrumental vaginal delivery-Diabetes in pregnancy (pre-existing type 1 or type 2 diabetes or gestational diabetes)-Pre-term delivery-Hypertensive disorders in pregnancy-Induction of labour-Augmentation of labour-Chorioamnionitis in labour-Unplanned hysterectomy-Blood transfusion-Admission to intensive care unit (ICU)-Trial of labour

Neonatal
-Birth weight >90th percentile-Birth weight <10th percentile-Apgar Score < 6 at 5 min-Assisted Ventilation immediately following delivery-Assisted ventilation required for more than 6 h-Neonatal intensive care unit (NICU) admission-Antibiotics received for suspected neonatal sepsis-Seizure or serious neurological dysfunction-Infant breastfed at discharge

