### Variables

Mean and standard deviation (SD) will be used to describe continuous variables if they are normally distributed, otherwise median, and interquartile range (IQR) will be used. Categorical variables will be reported as numbers and percentages.

Gestational BMI gain in kgm^-2^ will be reported in the primary analysis. GWG in kg will be analysed for the sensitivity analysis.

Variables will be measured/described as follows:-Gestational BMI gain in kgm^-2^ (for the main analysis). Analysed as a linear spline with a knot at 5 kgm^-2^ based on preliminary analysis of 2022 data.-Self-reported pre-pregnancy BMI in kgm^-2^ (based on height and self-reported pre-pregnancy weight) classified according to the Institute of Medicine (IOM) groups [15]-Measured BMI at birth in kgm^-2^ classified into groups of the same size as pre-pregnancy BMI to account for expected weight gain during pregnancy-GWG in kg (for the sensitivity analysis)-Parity (categorized as nulliparous, or parous)-Maternal age in years (as a continuous variable, with linearity observed in the preliminary analysis of the 2022 data)-Gestational age at birth in weeks (categorized by gestational week)-Maternal height in cm (as a continuous variable, with linearity observed in the preliminary analysis of the 2022 data)-Maternal race (to be categorized as the dataset allows)-Maternal cigarette smoking during pregnancy (to be categorized as the dataset allows)-Payment type (public/private)-Trimester of onset of maternity care (first/second/third trimester/no antenatal care)-Maternal education (categorized as (i) 8th grade or less, (ii) 9th-12th grade, no diploma, (iii) completed high school or GED, some college credit or associate degree, (iv) bachelor’s degree, (v) masters degree, doctorate or professional degree)-Any fertility treatment used in conception (yes, no, unknown)-Diabetes in pregnancy (to be categorized as the dataset allows)-Hypertensive disorders in pregnancy (to be categorized as the dataset allows)-Previous preterm birth (yes, no)

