### Analysis plan

Data will be downloaded from the CDC website (https://www.cdc.gov/nchs/data_access/vitalstatsonline.htm) for the most recent year with available data (2023 at the time of writing this protocol).

If data missingness for one or more explanatory or outcome variables occurs in > 5 % and < 40 % eligible births then multiple imputation will be considered. Potential mechanisms of missingness and the relationship of missingness to the outcome and covariates will be assessed when deciding to conduct multiple imputation or a complete case analysis.

If multiple imputation is required, we will use fully conditional specification with five imputed datasets. Any multiple imputation will include all explanatory and outcome variables, and any interaction terms. Interdependencies amongst variables will be handled with the passive imputation method. P-values for the likelihood ratio test for each variable in each imputed dataset will be pooled using the median p-value rule.

Using Robust Poisson Regression, maternal pre-pregnancy BMI will be modelled on the primary outcome of cesarean delivery and other covariates (listed below) excluding BMI gain during pregnancy. Maternal BMI at the time of delivery will be modelled on the same covariates. Of these two models, the model with the lowest Akaike Information Criterion (AIC) will be used to select the BMI variable with the greatest explanatory power to be used in subsequent analyses (either pre-pregnancy or delivery BMI). This variable is referred to as ‘Maternal BMI’ in all subsequent analyses below. The two models will also be compared using the log-likelihood test.

Pre-pregnancy BMI will be categorized according to the United States Centers for Disease Control and Prevention which classifies adult BMI as underweight (BMI < 18.5), normal weight (BMI 18.5 – 24.9), overweight (BMI 25-19.9), Class 1 obesity (BMI 30-34.9), Class 2 Obesity (BMI 35-39.9), and Class 3 Obesity (BMI 40 or more) [20]. Delivery BMI will be classified such that the same numbers of women will be in each class (i.e., the same quantile cut-offs will be used for pre-pregnancy and delivery BMI groups). This is expected to account for weight gain in pregnancy including factors such as fetal weight and amniotic fluid volume. Based on the exploratory analysis for 2022 data, BMI gain and gestational weight gain will be treated as linear splines with one knot placed at 5 kgm^-2^ and at 12 kg respectively.

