As nulliparous women are an important group who contribute to the first/primary cesarean delivery rate, we will test for interaction (effect modification) between maternal BMI gain and parity, and maternal BMI and parity. If interaction is present (BMI or BMI gain have a different association with cesarean delivery depending on parity), then the primary analysis will be restricted to nulliparous women only and we will conduct secondary analyses for parous women.

For the primary outcome of cesarean delivery, backward stepwise Robust Poisson Regression will be used. The following variables will be included in the multivariable Poisson regression model as potential predictors of cesarean section:•Maternal BMI (not eligible for exclusion in the backwards stepwise regression).•Gestational BMI gain (not eligible for exclusion in the backwards stepwise regression)•Parity•Maternal age (continuous)•Gestational age•Maternal height•Maternal race•Cigarette smoking•Payment type•Trimester of onset of maternity care (4 categories: first, second or third trimester, or no•antenatal care)•Education (categorized)•Fertility treatment used•Diabetes (3 categories: pre-pregnancy, gestational, none)•Hypertension in pregnancy (dichotomous)•Interaction terms: BMI x parity and BMI gain x parity

Birthweight will not be included as an explanatory variable because it was considered that fetal weight may be on the causal pathway between BMI or BMI gain and cesarean delivery. Therefore, the relative risks for BMI or BMI gain for the primary outcome of cesarean delivery will include any indirect effect mediated through fetal weight.

If Robust Poisson Regression Models do not converge then alternative regression methods will be considered.

For secondary outcomes, all explanatory variables will be retained in the model. Stepwise backward regression will not be used. No interaction terms will be used.

For the secondary outcome of third or fourth degree perineal laceration, the data will be limited to vaginal births only and the following covariates will be used: BMI at delivery, BMI gain, parity, maternal age, gestational age, maternal height, maternal race, mode of delivery (unassisted/vacuum/forceps).

For the secondary outcome of trial of labour, the following covariates will be used: BMI at delivery, BMI gain, parity, maternal age, gestational age, maternal height, maternal race, payment type, education, trimester of onset of maternity care, use of ARTs, and gestational diabetes.

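### The one-knot form for BMI gain rests on a shape check described only for cesarean, yet it is carried into the secondary outcomes without a re-check, where it could hide or reverse a low-gain association

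*Protocol article*

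**What the plan says.** The Protocol validation section describes how functional forms were explored: "Linearity was tested for continuous variables by plotting variable quantiles against the natural logarithm of the cesarean section rate". Its conclusion names two variables: "maternal height and maternal age were linearly associated with cesarean section and will be modelled in natural units". No other outcome is mentioned in that check.

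For BMI gain, the Variables section says: "Analysed as a linear spline with a knot at 5 kgm^-2^ based on preliminary analysis of 2022 data". The Analysis plan repeats this without limiting it to cesarean: "BMI gain and gestational weight gain will be treated as linear splines with one knot placed at 5 kgm^-2^ and at 12 kg respectively".

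For the other outcomes, the Analysis plan says "For secondary outcomes, all explanatory variables will be retained in the model" and "No interaction terms will be used". Several secondary outcomes are given the covariates of the primary model. Perineal laceration and trial of labour have their own lists, which also contain BMI gain. Rare outcomes with fewer than five events per variable may use a shorter list or a univariable model. The two sensitivity analyses replace BMI gain by weight gain in the primary analysis, or repeat the final imputed-data model in complete data. Neither examines shape for a secondary outcome.

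**The concern.** A form that suits the log cesarean rate says nothing about the form that suits a different outcome. The secondary list holds 12 maternal and 9 neonatal outcomes, 21 in all. It includes birth weight above the 90th and below the 10th percentile, two outcomes for which the relation to gain could well run in opposite directions.

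The planned spline can bend only once, at 5. Below 5, women who lose weight, gain little or gain a moderate amount all share one per-unit relative risk. If risk for some outcome falls and then rises again within that range, the single slope averages the two arms.

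BMI gain is listed under Primary study factors, so its coefficients are reported results and not just adjustment. The Uniqueness section hopes to temper expectations about limiting weight gain. That message depends on an accurate account of risk at low gain as well as high gain.

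**Working it through.** **Reading the text.** The only check described uses cesarean. The Variables section defines each form once, and the Analysis plan reuses the variables for the secondary outcomes with no re-check, other knot or flexible term. That the knot at 5 was judged against cesarean is an inference from reading Variables and Analysis plan together with Protocol validation. The sentence that states linearity names only age and height.

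The plan gives no figure to reproduce on this point, so the check is whether the planned form can mislead, and by how much.

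**Assumptions (none is in the documents).** The true log relative risk is c × (gain − t)², where t is the gain of lowest risk. BMI gain is normal with mean/SD 4.5/2.0, 4.5/2.5 or 4.0/3.0 kg/m2. The planned two-slope Poisson model with a knot at 5 was fitted to 400,000 simulated births per setting.

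**Formulas.** True RR of gain a versus b = exp{c[(a − t)² − (b − t)²]}. For a and b at or below 5, fitted RR = s^(a − b), where s is the fitted relative risk per unit below 5.

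**Turn at t = 2, c = 0.02.**
- True RR, −2 versus 5: exp{0.02 × (16 − 9)} = exp(0.14) = 1.15.
- True RR, −2 versus 2: exp(0.02 × 16) = 1.38. This comparison does not use the knot as reference.

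| Gain mean/SD | s (95% CI) | Fitted, −2 v 5 (true 1.15) | Fitted, −2 v 2 (true 1.38) |
|---|---|---|---|
| 4.5/2.0 | 1.029 (1.020 to 1.038) | 1.029^(−7) = 0.82 | 1.029^(−4) = 0.89 |
| 4.5/2.5 | 0.997 (0.990 to 1.004) | 0.997^(−7) = 1.02 | 0.997^(−4) = 1.01 |
| 4.0/3.0 | 0.968 (0.963 to 0.973) | 0.968^(−7) = 1.26 | 0.968^(−4) = 1.14 |

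The first row reverses the association with an interval that excludes 1 (a separate refit gave 0.84 in place of 0.82). The second row reports almost nothing below 5. The third gets the direction at −2 right.

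**Weaker curve, t = 2, c = 0.01, mean/SD 4.5/2.0.** s = 1.012 (1.003 to 1.021). At −2 versus 5 the truth is exp(0.07) = 1.07 and the fit 0.92.

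**Turn at t = 3, c = 0.02, mean/SD 4.5/2.0.** At −2 versus 5 the truth is exp{0.02 × (25 − 4)} = 1.52 and the fit 1.15. At 2 versus 5 the truth is exp{0.02 × (1 − 4)} = 0.94 and the fit 1.06.

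**Turn at the knot, t = 5, c = 0.02, mean/SD 4.5/2.0.** At −2 versus 5 the truth is 2.66 and the fit 2.01. At 8 versus 5 the truth is 1.20 and the fit 1.34. The direction is right on both sides and only the sizes are off.

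**Age as a covariate.** The assumed log relative risk for age was 0.003 × (age − 29)², with a true relative risk of 1.051 per unit of gain and assumed linear age–gain correlations of 0, −0.1, −0.2 and +0.2. With age entered as one line, the fitted gain effect lay between 1.047 and 1.056. In further runs the largest shift was to about 1.04.

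**The case against.** The strongest reply is that nothing in the documents shows a U-shaped risk for any secondary outcome. Every size above comes from an assumed curve. The spline is already non-linear, and a U that turns near 5 keeps its direction. This stands, and it confines the point to what the form can do.

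Second, relative risks quoted against a gain of 5 exaggerate the misfit, because the knot is the worst-fitting point of the central range. In one refit (turn at 3, c = 0.02, mean 4.8, SD 2.4), fitted absolute risk was about 10% low at 5 but within about 7% of truth at gains of 0 to 4, 6, 8 and 10. This also stands. The comparison of −2 with 2 avoids that reference and still fails under a turn at 2. However, −2 lies far out: (−2 − 4.5)/2.0 = −3.25 SD in the first setting and (−2 − 4.0)/3.0 = −2 SD in the third.

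Third, a reader might infer that linear age and height leave serious residual confounding. Both are covariates, not study factors, and the age runs moved the gain effect little. Height was not computed. This is a minor check only.

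Fourth, a reader might infer that all 21 outcomes are misreported. That is too broad: rare outcomes may use reduced models, and trial of labour is closely tied to cesarean.

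Last, an article may leave model checking to a fuller plan. Here, though, the article itself fixes the form and gives its justification, and the check it describes covers one outcome. That part of the reply does not hold.

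**Conclusion.** The concern holds for BMI gain in the secondary outcomes. The form is fixed for a primary study factor on a check described only for cesarean, and nothing in the plan would reveal a poor fit elsewhere. If risk turns below 5 kg/m2, the slope below the knot can be flat or reversed: with a turn at 2, it is about 1.00 or 1.03 per unit in two of three assumed gain distributions. If risk turns near 5, direction is preserved. These sizes rest on log-quadratic curves and normal gain distributions that the documents do not supply.

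The documents do not support saying that any secondary result will be wrong, that age or height materially bias the gain effect, or that the primary cesarean analysis is affected. The point is worth acting on because the check is cheap and can be finished before the results are seen.

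**What to change.** Before opening the 2023 data, repeat the Protocol validation plot in the 2022 data for BMI gain against each non-rare secondary outcome. Split the lowest quantiles finely enough to separate weight loss from low gain. Plot age and height in the same way as a minor check.

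Where the one-knot form fits, keep it and say so. Where it does not, prespecify an outcome-specific knot or a restricted cubic spline for BMI gain, and report relative risks at set gain values that include weight loss and low gain. Keep the knot at 5 for cesarean. For rare outcomes, keep the simple form and state that its shape was not checked.

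The cost is some extra plotting in data already in hand, a few more model terms for some outcomes, and results less compact than two slopes. Flexible splines on all three variables for every outcome would be a defensible preference but are not required.

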## Limitations

Limitations include the retrospective study design using administrative data, limiting the available variables. Misclassification and under-reporting of complications are potential concerns, although caesarean section is unlikely to be missed by reporting clinicians and the birth certificate worksheet. We have no reason to suspect any mis recording of maternal weight and height but this is possible. Maternal pre-pregnancy weight is self- reported, but we do not expect any under or over reporting of pre-pregnancy weight to be related to the primary outcome of cesearean delivery.

## Uniqueness of the study

This study is unique in that it will explore whether it is BMI rather than GWG that is linked to cesarean birth and other outcomes. Given the limited efficacy of interventions during pregnancy in modifying GWG, the study will be able to examine how BMI influences outcomes and possibly acts through mechanisms independent of GWG. This has the potential to add evidence that challenges the foundational assumptions underpinning much of the existing literature on GWG. While promoting healthy nutrition and physical activity during pregnancy remains beneficial, the study may support a better allocation of health care resources and reduce unrealistic expectations in women with regard to limiting GWG.

## Data Availability

Data will be made available on request.
